### A brief overview of the trial

The COgNitive Therapy for depRessiOn in tubercuLosis treatment (CONTROL) trial aims to address the dual burden of TB and depression in Pakistan [15]. It is a pragmatic parallel arm (intervention and control arm), randomized controlled trial (RCT) conducted across TB treatment centers in Khyber Pakhtunkhwa (KP), Pakistan, evaluating the clinical and cost-effectiveness of CONTROL intervention in a randomised controlled trial [15]. In these TB centers, the program is implemented through the Directly Observed Therapy Short Course (DOTS) strategy, ensuring structured service delivery to patients. The CONTROL CBT-based intervention aims to improve the outcomes both for depression and TB in people with TB and MDR-TB. The trial tests its effectiveness and cost-effectiveness and examines how the intervention can be implemented in the real-world setting of the Provincial TB Control Programme, KP (PTP-KP) in Pakistan [15]. Patients in the intervention arm receive both Enhanced Treatment as Usual (ETAU) and the CBT intervention, whereas patients in the control arm receive only ETAU. The ETAU treatment includes the Mental Health Gap Action Programme (mhGAP). In this model, TB health workers (TBHWs)—non-specialist healthcare providers already engaged in TB care and also called TB DOTS facilitators—are trained to deliver CBT sessions to TB patients diagnosed with depression. This approach allows for the efficient use of available resources and ensures that patients can access mental health care within their existing care pathways. Participants in the CONTROL intervention group will undergo six sessions of a CBT-based intervention; the content and modes of intervention were adapted based on the Southampton framework used previously in Pakistan [16]. The Southampton Adaptation Framework is utilized to culturally adapt CBT by considering a patient’s cultural background and religious affiliation, thereby enhancing mental health outcomes [17]. This framework concentrates on three main areas: awareness of culture and religion, assessment and engagement with cultural issues, and modifications in therapy to align with local values and norms [17]. CBT therapy aims at addressing depression while also employing problem-solving and motivational techniques to improve compliance with ATT. Each therapy session will be conducted one-on-one, lasting between 40 and 60 min [15]. The design and methodology of the CONTROL trial are detailed in its published protocol [15], while this paper focuses on the methodology used for the process evaluation of the CONTROL trial.

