### Quantitative data

Quantitative data collection for the process evaluation will systematically measure key implementation outcomes related to integrating mental health screening and CBT therapy within the routine TB control program in KP, Pakistan. Data will be collected using routine trial logs (Excel sheets consisting of prescreening, screening, recruitment data, retention data, and CBT records), structured checklists and questionnaires, patient records, and fidelity assessment tools.

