### Data collection tools

Acceptability, appropriateness, and feasibility of the CONTROL study and CBT intervention will be assessed at 8 weeks post-randomization using three valid and reliable scales developed by Weiner et al., the Acceptability of Intervention Measure (AIM), Intervention Appropriateness Measure (IAM), and the Feasibility of Intervention Measure (FIM) [26]. For sampling, measuring tools, and data collection time points, see Table 2. Each scale consists of four thematic questions with five responses ranging from “completely disagree” to “completely agree” on a five-point Likert scale [27]. Selected for their conceptual distinctiveness, AIM, IAM, and FIM provide valuable insights into the implementation process while also accounting for potential empirical interrelations [27]. They enhance the evaluation by providing robust, evidence-based metrics to assess the feasibility and acceptability of the intervention in complex healthcare settings [27].

**Table 2 Tab2:** Implementation outcomes for CONTROL trial process evaluation

Quantitative measures					
**Sr. No**	**Outcomes**	**Brief description**	**Measuring tool**	**Data collection timepoint**	**Group (patients, therapist, trial team)**
**1**	**Appropriateness**	Appropriateness refers to the perceived fit, relevance, compatibility, suitability, usefulness, and practicability of the CBT intervention within the TB care settings, as experienced by facilitators and participants	Intervention Appropriateness Measure (IAM)	8-week	10% of randomly selected patients in the intervention arm
			The Applied Mental Health Research Group (AMHR)-appropriateness subscale	8-week	10% of randomly selected patients in the intervention arm
**2**	**Feasibility**	The CBT intervention’s actual fit, utility, and practicability within routine TB care, assessing the extent to which TBHWs can effectively deliver CBT and patients can access and engage with it given the available resources, time, and training	Feasibility of Intervention Measure (FIM)	32-week	All trial staff (DOTS and the trial team)
			The Applied Mental Health Research Group (AMHR)- feasibility subscale	8-week	10% of randomly selected patients in the intervention arm
			% assigned to the intervention who agreed to enroll in the trial	After the definitive trial, all relevant data will be retrieved from the trial team’s data logs	

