### Data collection and sampling

The above quantitative measures will be applied to collect data from the intervention group. The process evaluation will involve a carefully selected population from various groups, including patients, CBT therapists (TBHWs), and trial staff, to ensure comprehensive representation and validity of findings.

Data collection from all TBHWs and trial staff will utilize FIM. Research assistants from the process evaluation team will facilitate the completion of the tool by TBHWs and trial staff at the 32-week post-randomization mark, ensuring standardized and accurate data collection. The IAM and AIM will assess 10% of patients who have completed therapy sessions. Data collection will occur 8 weeks after randomization by the research assistants. The tools (FIM, IAM, AIM) will be translated into the local language to ensure cultural and linguistic relevance.

The AMHR subscales for appropriateness, adoption, feasibility, and acceptability will be administered to 10% of randomly selected patients in the intervention arm at 8 weeks post-randomization. The AMHR tool will be updated based on the CVI results and subsequently translated into the local language.

Retention rates, encompassing the number of sessions attended and the proportion of participants who discontinued the intervention, will be systematically evaluated [15]. Furthermore, the enrollment rate, defined as the percentage of individuals assigned to the intervention who consented to participate, will also be analyzed. These data will be extracted from the trial logs upon the completion of the definitive trial, offering valuable insights into participant engagement, adherence, and overall intervention feasibility and acceptability [15].

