## Data analysis

### Quantitative data analysis

We will employ descriptive and inferential statistical methods to analyse the CONTROL study and CBT intervention’s implementation outcomes—acceptability, appropriateness, adoption, and feasibility. Data from the AIM, IAM, FIM, and AMHR scales will be analysed to assess central tendencies and variability. Regression analyses will be conducted to explore relationships between implementation outcomes and participant characteristics. Retention and enrolment rates will be calculated as proportions, with chi-square tests to examine group differences.

Two independent reviewers, both experts in CBT, will assess a randomized selection of 10% of the audio-recorded CBT sessions to analyse the fidelity of the CONTROL CBT intervention through CTS-R and a CBT delivery assessment checklist. According to the Newcastle Cognitive Therapy Centre, a minimum competence standard is set at 36, with higher scores indicating greater therapeutic competence. Descriptive statistics will summarize the distribution of scores across sessions, and inter-rater reliability will be assessed using intraclass correlation coefficients to ensure consistency between reviewers. Similarly, the delivery assessment checklist evaluates adherence to the intervention’s content, and for each session, item scores will be aggregated to produce a total adherence score. Descriptive statistics will describe the adherence levels, and inter-rater reliability will be calculated to confirm reviewer consistency.

Penetration analysis will calculate the proportion of TB patients screened with the PHQ-2 and those referred for mental health services. High screening and referral rates will indicate successful penetration of mental health assessments into the TB program. Cost analysis will utilize data from the CSRI to compute the total and per-patient costs of implementing the mental health interventions. This will include direct costs (e.g., training, therapy sessions) and indirect costs (e.g., patient travel, lost productivity). The cost-effectiveness of the intervention will be evaluated by comparing the incremental costs to the health outcomes achieved, such as reductions in depression and anxiety symptoms.

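### The enrolment rate is taken among patients already assigned to the intervention, so if consent precedes randomisation it is 100% by construction and says nothing about acceptance or refusal

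*Protocol article*

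**What the plan says.** The enrolment rate is defined twice. Under Acceptability, appropriateness, adoption and feasibility, the Data collection and sampling section gives it as "the enrollment rate, defined as the percentage of individuals assigned to the intervention who consented to participate". The feasibility row of Table 2 gives it as the percentage "assigned to the intervention who agreed to enroll in the trial". Both take it from the trial team's logs after the definitive trial. It is the only log-based entry in that row; the other two are questionnaires (FIM and the AMHR feasibility subscale).

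Retention is defined in the same text section: "Retention rates, encompassing the number of sessions attended and the proportion of participants who discontinued the intervention, will be systematically evaluated".

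The Quantitative data analysis section then plans: "Retention and enrolment rates will be calculated as proportions, with chi-square tests to examine group differences". It does not say which groups.

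Three other statements bear on this:

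- The overview of the trial describes a parallel-arm randomised design and says that CBT goes to the intervention arm, "whereas patients in the control arm receive only ETAU".
- The Quantitative data section lists prescreening, screening and recruitment records among the logs.
- The article does not give the order of consent and randomisation. It refers to the published trial protocol for trial methods.

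**The concern.** An enrolment rate is useful when its denominator is the people who were offered the trial and its numerator is those who accepted. Here the denominator is people already assigned to one arm. If consent comes first, refusals have left before the denominator is counted, so the ratio cannot vary.

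The evaluation is meant to inform scale-up in the provincial TB programme, and the article says that these log data will give insight into engagement, feasibility and acceptability. A figure fixed by its own definition cannot do that, and a reported 100% could be misread as universal acceptance. The chi-square test planned on the same figure would have nothing to test. For retention, the open question is which groups are meant, since control patients have no CBT sessions to attend or discontinue.

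**Working it through.** The article states no enrolment figure, so there is nothing to reproduce. The check applies the definition as written.

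**1. Could the rate mean uptake of CBT after allocation?** The text version speaks of consenting to participate, which alone might allow that reading. Table 2 speaks of agreeing to enrol in the trial, which does not. Both therefore describe trial enrolment among people already assigned.

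**2. Value of the rate.**
- Formula: rate = (assigned to intervention and consented) / (assigned to intervention).
- Assumption: consent precedes randomisation, so the numerator equals the denominator.
- Arm size: the fidelity sampling section takes 10% of IDs, giving 35 per session, so the implied arm is 35 / 0.10 = 350. This is derived, not stated, and the conclusion does not depend on it.
- Result: 350 / 350 = 100%.

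If consent followed assignment, the rate could fall below 100%.

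**3. Chi-square test on enrolment.** Split the 350 into any two groups, say 175 and 175 (assumed):

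| | Group A | Group B | Total |
|---|---|---|---|
| Enrolled | 175 | 175 | 350 |
| Not enrolled | 0 | 0 | 0 |

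The expected count in each lower cell is 0 × 175 / 350 = 0. The contribution (O − E)² / E is then 0/0, and the statistic is undefined. The same happens for any other grouping, because the lower row is always empty.

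**4. Chi-square test on retention.** Retention is counted in CBT sessions and in discontinuation of the intervention. The control arm has neither, so a two-arm table cannot be formed. A table within the intervention arm can. Illustration, with assumed figures of 175 patients per district and completion of 140/175 (80.0%) against 123/175 (70.3%):

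χ² = 350 × (140 × 52 − 123 × 35)² / (263 × 87 × 175 × 175) = 4.42, 1 df, p = 0.036.

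The test works once its groups are named.

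**5. What a usable denominator would show.** Assume 1:1 allocation, so 2 × 350 = 700 randomised, and let the number of eligible patients invited vary (none of this is stated in the article):

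| Eligible and invited | Rate as redefined | Rate as written, consent first |
|---|---|---|
| 800 | 700/800 = 87.5% | 100% |
| 900 | 700/900 = 77.8% | 100% |
| 1,000 | 700/1,000 = 70.0% | 100% |
| 1,400 | 700/1,400 = 50.0% | 100% |

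**The case against.** Four points can be made for the plan.

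**The order of consent and assignment is not stated.** This stands. The article leaves trial methods to a publication that is not shown, so 100% is conditional and not a fact that the article establishes. Consent first is nonetheless usual in such a design, and nothing in the article describes consent after assignment.

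**The chi-square need not be between arms.** A reader might infer that the tests have no groups to compare at all. The documents do not support that. The analysis section speaks only of group differences and never mentions the arms. The article describes two districts, 12 facilities, three levels of care, and patients with TB or MDR-TB. For retention the groups are unnamed, not absent, and an article may leave that detail to a fuller document. The enrolment test fails for a different reason: the rate has no variation.

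**The restriction to the intervention group is not as explicit as it may look.** The sentence "The above quantitative measures will be applied to collect data from the intervention group" opens its section and most naturally refers to the questionnaires just described. That retention applies only to CBT recipients follows from how it is defined, not from this sentence.

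**Feasibility does not rest on this one figure.** A reader might also infer that the evaluation would report perfect feasibility whatever happened. That goes too far. The FIM, the AMHR feasibility subscale and the qualitative work also address feasibility, and the penetration section plans counts of patients screened, further assessed and given CBT, with referral and dropout rates. The stated gap is narrower: no planned measure gives consent among eligible patients who were invited.

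**Conclusion.** The point holds for the denominator. Both definitions count enrolment among people already assigned to the intervention. If consent precedes randomisation, the indicator is 100% by construction, carries no information on acceptance or refusal, and leaves the enrolment chi-square uncomputable. In the illustration, true acceptance anywhere from 50.0% to 87.5% would be reported as 100%. That range rests on an assumed 700 randomised and assumed numbers invited; the article gives neither.

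The retention point is smaller. As defined, session-based retention cannot be compared between the two arms, but it can be compared within the intervention arm.

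This is not detail left to another document, since the article fixes the definition itself, in two places. It concerns one descriptive indicator of the process evaluation and does not touch randomisation or the trial's effectiveness outcomes.

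**What to change.** - **Enrolment rate.** In Table 2 and in the data collection text, define it as patients who consented and were randomised divided by eligible patients invited. Take the counts from the "routine trial logs (Excel sheets consisting of prescreening, screening, recruitment data, retention data, and CBT records", after confirming that the logs record refusals.
- **CBT uptake.** Report it as a separate indicator: patients attending at least one session divided by patients randomised to CBT.
- **Order of consent and randomisation.** State it, so that both rates can be interpreted.
- **Chi-square tests.** In the analysis section, name the groups. For session-based retention use groups within the intervention arm, for example district or level of care, and not the two arms. With the new denominator, enrolment can also be compared across districts or facilities.

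The cost is wording in Table 2 and two text sections. The data are to be extracted only after the definitive trial, so the change requires no new collection if refusals are already logged; if they are not, logging them has to start now. The downside is that the reported enrolment figure falls below 100% as soon as any eligible patient declines.

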## Fidelity

### Data collection tools

CBT sessions will be audio recorded to evaluate the fidelity to CONTROL CBT intervention delivery using the Revised Cognitive Therapy Scale (CTS-R) and CBT delivery assessment checklist (CDAC). These two tools will comprehensively evaluate fidelity, assessing therapeutic competence and adherence to intervention content (Table 2).

The CTS-R is a well-established instrument for assessing therapists’ competence in delivering CBT [32]. The scale comprises 12 items, evaluating several key aspects ranging from agenda setting to homework setting. Each item is scored on a 7-point Likert scale ranging from 0 to 6, where 0 indicates “the absence of a competence feature or highly inappropriate performance” and 6 indicates “excellent performance, or very good even in the face of patient difficulties” [32]. These items are categorized into three main sections: general interview procedures, interpersonal effectiveness, and specific cognitive-behavioral techniques. This structured approach ensures a comprehensive assessment of both the therapeutic process and the delivery of CBT techniques. The maximum score on the scale is 72 (12 × 6). The Newcastle Cognitive Therapy Center has set a minimum competence standard of 36, an average of 3 marks per item [32].

The second tool that will be used to measure fidelity is the CBT delivery assessment checklist; this will evaluate how the intervention content components were delivered and the degree of adherence. The checklist was developed by CBT master trainers based on the CBT content and was subsequently validated by CBT experts FN and MG. It was piloted and modified for use in the definitive trial. Each item on the checklist is marked on a 5-point Likert scale from 0, “not implemented,” to 4, “fully implemented.”

### Data collection and sampling

The audio recordings of each CBT session will be assessed by two trained independent raters (experts in CBT) to ensure adherence to the intervention protocol using CTS-R and the CBT delivery assessment checklist. A randomization procedure, without replacement [33], is applied to randomly select 10% of the IDs for each CBT session, resulting in 35 participant IDs per CBT session; 210 sessions will be recorded. We will utilize randomization without replacement to ensure unbiased and representative audio selection for fidelity assessment. This method guarantees each session has an equal chance of selection, preventing the overrepresentation of specific facilitators and enhancing fairness across all sessions. Research assistants responsible for recording CBT sessions will undergo structured training to ensure adherence to the standardized protocol for session documentation. Informed consent will be obtained from all participants before recording.

## Penetration, sustainability and implementation costs

### Data collection tool

Penetration and sustainability will be assessed using routine trial logs after the definitive trial, focusing on policymakers’ acceptance of mental health measures and evaluating the sensitivity and specificity of the Patient Health Questionnaire short version (PHQ-2) in routine depression screening within the TB care program. In the CONTROL definitive trial, TBHWs will (pre)screen all patients presenting at the selected TB centers on PHQ-2 and assess the frequency of depressed mood and anhedonia over a 2-week period. Being a simple two-question screening tool, it will be easy to implement in the routine, and could be used by healthcare workers at TB centers [15]. The data will also help explore the potential adaptation of PHQ-2 to screen depression in other chronic infections prevalent in the region, providing robust insights into the implementation and scalability of the study measures across diverse healthcare settings.

Implementation costs are influenced by three main factors: the treatment’s complexity, the implementation strategy’s intricacy, and the setting where the treatment is delivered. Consequently, the total cost of implementation depends on the specific intervention, the chosen strategy, and the delivery environment [23]. Implementation costs will be measured using the Client Service Receipt Inventory (CSRI) [34]. The evaluation will mainly be approached from the standpoint of the health system, including (a) expenses associated with the implementation of the intervention during the trial, (b) utilization of additional healthcare and related services by the participants, and (c) costs incurred by patients and their families.

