### Data collection and sampling

Data collection will include routine trial logs to document the number of TB patients screened, further assessed, and those receiving CBT intervention. Screening penetration will be measured by calculating the proportion of TB patients screened using PHQ-2 and their referral rates to mental health services. Usability and sustainability will be assessed by recording the time required to complete PHQ-2 screening, dropout rates, and follow-up adherence among CBT recipients.

The expenses related to the implementation will be evaluated by examining the costs and cost-effectiveness measures used during the trial. This evaluation will consider the expenses of the CONTROL intervention and enhanced treatment as usual (ETAU). An adapted version of the Client Service Receipt Inventory (CSRI) will be utilized to assess costs, similar to our previous methodology for cost-effectiveness analysis of psychological intervention in the region [35]. This assessment will encompass visits to primary care and outpatient services, medication costs, travel time, transportation expenses, and days lost from work. Current prices or unit costs will be obtained from national sources, validated, and, if necessary, extrapolated from UK equivalents to be applied to these resource categories, allowing for an estimate of overall and individual costs.

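### PHQ-2 sensitivity and specificity are to come from trial logs in which PHQ-2 is the entry screen, and the protocol article describes no reference diagnosis for PHQ-2 negatives

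*Protocol article*

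**What the plan says.** The commitment is in the protocol article, section on penetration, sustainability and implementation costs, under Data collection tool. It names the source, "Penetration and sustainability will be assessed using routine trial logs after the definitive trial", and the same sentence gives as one focus "evaluating the sensitivity and specificity of the Patient Health Questionnaire short version (PHQ-2) in routine depression screening within the TB care program". The next sentence sets the role of PHQ-2 in the trial: "TBHWs will (pre)screen all patients presenting at the selected TB centers on PHQ-2".

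Three other places bear on what the logs can hold:

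- Quantitative data describes them as "Excel sheets consisting of prescreening, screening, recruitment data, retention data, and CBT records".
- Data collection and sampling, in the same penetration section, says they will be "routine trial logs to document the number of TB patients screened, further assessed, and those receiving CBT intervention".
- The brief overview of the trial says that TB health workers "are trained to deliver CBT sessions to TB patients diagnosed with depression". It does not name the instrument that makes the diagnosis.

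No section names a reference standard against which PHQ-2 is to be judged, or says that PHQ-2 negatives, or a sample of them, receive a diagnostic assessment.

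**The concern.** Sensitivity is the share of depressed patients whom the screen detects, so it needs a count of depressed patients whom the screen missed. Specificity needs a count of non-depressed patients whom the screen cleared. Both counts lie among PHQ-2 negatives. If the reference assessment follows only a positive screen, neither count is in the logs. This is partial verification, and a larger sample does not cure it.

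What is at stake is a figure that would look like evidence on screening performance but would be produced by the patient flow. A sensitivity of 100% would hide the missed cases that matter to a programme considering PHQ-2 for routine use. Timing adds to this: the logs are read after the definitive trial, and assessments never made in negatives cannot then be recovered from them.

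**Working it through.** **The plan's own figure.** The article states no value for PHQ-2 accuracy, so there is nothing to reproduce. The check is whether the described data can yield the planned quantities.

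**What the funnel would observe.** Let TP and FP be PHQ-2 positives with and without depression on the reference assessment, and FN and TN the same for PHQ-2 negatives.

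- Sensitivity = TP/(TP + FN)
- Specificity = TN/(TN + FP)
- Positive predictive value (PPV) = TP/(TP + FP)

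If all positives and no negatives are assessed, TP and FP are known, but for negatives only the sum FN + TN is known. PPV can be estimated. The other two cannot be point-estimated without an outside assumption about depression among negatives.

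**The two obvious shortcuts.**

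- Assessed patients only: sensitivity = TP/(TP + 0) = 100%; specificity = 0/(0 + FP) = 0%.
- All unassessed negatives counted as not depressed: FN = 0, so sensitivity is again 100%. TN takes its largest possible value, so specificity is reported at its upper bound.

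**Size, on assumed counts.** None of these counts is in the article: 1000 prescreened, 300 positive, 200 of those confirmed (TP = 200, FP = 100), 700 negative. Let f be the unknown depressed share of the negatives. Then sensitivity = 200/(200 + 700f) and specificity = 700(1 − f)/(700(1 − f) + 100).

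| f | Sensitivity | Specificity |
|---|---|---|
| 0% | 200/200 = 1.00 | 700/800 = 0.875 |
| 5% | 200/235 = 0.85 | 665/765 = 0.869 |
| 10% | 200/270 = 0.74 | 630/730 = 0.863 |
| 20% | 200/340 = 0.59 | 560/660 = 0.848 |
| 30% | 200/410 = 0.49 | 490/590 = 0.831 |
| 100% (logical limit) | 200/900 = 0.22 | 0/100 = 0 |

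The same logged data fit every row. PPV is 200/300 = 0.67 throughout.

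**PPV does not stand in for accuracy.** PPV = prev × Se/(prev × Se + (1 − prev)(1 − Sp)). Taking sensitivity/specificity of 75/85% or 90/70% and prevalence of 20% to 50%, all assumed:

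- Lowest: 0.2 × 0.9/(0.2 × 0.9 + 0.8 × 0.3) = 0.18/0.42 = 0.43
- Highest: 0.5 × 0.75/(0.5 × 0.75 + 0.5 × 0.15) = 0.375/0.45 = 0.83

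PPV is useful to a screening programme, but it depends on prevalence and should be reported as PPV.

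**What verifying some negatives would give.** Keep the same counts, with f = 10% found in a random sample of the negatives. The standard error of f is √(f(1 − f)/m × (1 − sampling fraction)), with m negatives assessed.

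- 10% sampled (m = 70): f is 0.033 to 0.167; sensitivity 0.74 (about 0.63 to 0.90); specificity 0.86 (about 0.85 to 0.87).
- 20% sampled (m = 140): f is 0.056 to 0.144; sensitivity 0.74 (about 0.66 to 0.84); specificity 0.86 (about 0.86 to 0.87).

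These intervals reflect sampling of the negatives only.

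**The case against.** The strongest objection is that the premise is inferred. Nowhere does the article say that PHQ-2 negatives stop at the prescreen. It does not say who is assessed further, and the list of log contents is not a rule for moving between stages. The parent trial's design is left to its own published protocol, which is not shown and could describe assessment of some negatives. This stands. A reader might infer that screen-negatives have no reference diagnosis; the article supports only that it describes none. The point must therefore be conditional. It is still more than omitted detail, because the article itself pairs these two quantities with a source that, as described, cannot supply them.

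Four further limits also stand:

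- Quantitative data analysis gives only proportions: "Penetration analysis will calculate the proportion of TB patients screened with the PHQ-2 and those referred for mental health services". A reader might count the absence of an accuracy analysis as a fault in itself. It is not, since such detail is commonly left to a fuller plan.
- A reader might infer that the case for routine PHQ-2 use, or for adapting it to other chronic infections, rests on the accuracy figure. The article rests routine use on the simplicity of the tool, and says only that the data will help explore adaptation.
- Specificity suffers much less than sensitivity. In the illustration it moves by 0.044 (0.875 to 0.831) for f up to 30%. The 100%/0% pair arises only if accuracy is computed on assessed patients alone, which no section proposes.
- PPV is not guaranteed either. The listed counts include no diagnostic result, and a valid PPV needs all positives, or a representative subset, to have been assessed.

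**Conclusion.** The concern holds conditionally. As described, the logs do not support the planned sensitivity and specificity. If only PHQ-2 positives are assessed further, sensitivity is not estimable and is 100% by construction under either shortcut, while specificity can only be bounded. On the assumed counts, the logical range is 0.22 to 1.00 for sensitivity and 0 to 0.875 for specificity. The conclusion rests on reading the sequence of log stages as a funnel that negatives leave at PHQ-2. That is a strong inference, and the parent protocol could overturn it.

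Severity is moderate. A reader might infer that the penetration or sustainability outcomes fail with this clause, but they do not. Accuracy is not named in the four objectives, in the penetration and sustainability rows of Table 2, or in the analysis section. Penetration is measured by the proportions screened and referred, and sustainability by screening time, dropout and follow-up adherence. None of these depends on a reference diagnosis in PHQ-2 negatives.

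**What to change.** In Data collection tool, under penetration, sustainability and implementation costs, replace sensitivity and specificity with the following, each with a 95% confidence interval:

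1. the proportion of prescreened patients who are PHQ-2 positive;
2. the proportion of PHQ-2 positives who complete the further assessment;
3. where the logs hold the result of that assessment, the PPV of PHQ-2 against it, naming the assessment and saying whether all positives received it.

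State that sensitivity and specificity are not estimable from these logs.

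Keep them only if the parent trial already applies the reference assessment to all PHQ-2 negatives or to a random subset. In that case name the reference standard, say how the negatives were chosen and, if only a subset was assessed, weight each assessed patient by the inverse of the probability of being assessed.

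The cost is a change of wording, plus a check of what the logs record. No new data collection is needed. The price is a narrower claim about PHQ-2, covering yield and predictive value in these centres but not detection of all depressed patients.
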